### Ethical approval

The study is undertaken in accordance with the declaration of Helsinki (http://www.wma.net/en/30publications/10policies/b3/index.html), the applicable Dutch legislation and in agreement with the Conduct Health Research (version 2005; http://www.federa.org/gedragscodes-codes-conduct-en). It has been assessed by the Medical Ethics Committee of the region Arnhem-Nijmegen in the Netherlands. According to Dutch legislation and the committee, the study can be carried out without a review procedure by the committee because residents are not actively involved in data collection for the study, all resident data consist of observations made by the nursing staff. In addition, approval is asked from the local ethics committees of participating Nursing Homes.

Legal representatives are informed about the study and the aim to include the resident in the study, and are given the opportunity to refuse. Representatives are also informed that they can withdraw their relative at any moment in the study. Nursing staff provided informed consent before filling in the questionnaires on the website.

### Data analysis

Statistical analysis will be performed using the Statistical Package for Social Sciences (SPSS). The UBOS score will be used as primary outcome and emotional workload, work satisfaction, stress reactions at work and knowledge about challenging behavior as secondary outcomes for nursing staff in an ANCOVA analysis in which outcome score is the score after intervention controlling for the score before the intervention. Age, sex and time working on the unit will be used as covariates. The NPI-NH and the CMAI will be used as outcomes for the residents. Age, sex and length of stay will be used as covariates. For the primary and secondary outcome analyses, multilevel linear regression and multilevel logistic regression analyses on units, individual nurses and residents will be used [85]. These analyses will calculate effects on distress (NPI, UBOS), challenging behavior (NPI-NH, CMAI), quality of life of residents (Qualidem, RISE), and perceived quality of care.

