### Sample size

For calculating the appropriate sample size we use the following assumptions:

DSCU consist of 20 residents on average [49], with 18 nursing staff on average eligible for inclusion.

For the primary outcome, stress experienced by nursing staff, we assume that our intervention leads to a 4 point decrease on the subscale Emotional Exhaustion of the Maslach Burnout Inventory based on the reduction found by Yun-Hee Jeon et al. [83] who found a reduction of 2.5 points after three months and 4.4 points after nine months in her study in which she used training and support to evaluate person centred care to dementia care mapping and usual care. Based on these assumptions and based on a significance level alpha of 0.05, a power of 0.80 and a conservative estimated correlation between two measurements of .6 [84] and an ICC of 0.05 we need a sample size of 121 nursing staff members and 121 residents in each group for ANCOVA analysis based on equal sample sizes which implies including 16 clusters; eight intervention and eight control units. In order to account for intra cluster correlations, Multi Level Analysis will be used. Nursing staff that moves to another job will be replaced, the nursing staff replacing them will join in the course. To compensate for nursing staff not replaced in time we will add an extra unit so we use nine intervention and nine control units this results in 135 nursing staff members and 135 residents in the intervention group and an equal amount in the control group.

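### The data analysis section states baseline adjustment for staff outcomes but leaves the baseline score off the resident covariate list, although residents are sized for ANCOVA

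*Protocol article*

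**What the plan says.** The Sample size section gives one calculation. It rests on the staff primary outcome: "we assume that our intervention leads to a 4 point decrease on the subscale Emotional Exhaustion of the Maslach Burnout Inventory". It is "based on a significance level alpha of 0.05, a power of 0.80". Clustering enters through an ICC of 0.05, and the repeated measurement enters as "a conservative estimated correlation between two measurements of .6". The result is applied to both populations: "we need a sample size of 121 nursing staff members and 121 residents in each group for ANCOVA analysis". One unit per arm is then added, which gives nine units and 135 residents per arm.

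The Data analysis section defines the ANCOVA in a sentence about the UBOS and the "secondary outcomes for nursing staff in an ANCOVA analysis in which outcome score is the score after intervention controlling for the score before the intervention". The staff covariates are listed next: time on the unit, age and sex. Residents get sentences of their own: "The NPI-NH and the CMAI will be used as outcomes for the residents. Age, sex and length of stay will be used as covariates". The section then says that multilevel regression will be used for primary and secondary outcomes, and it brings in the Qualidem, the RISE and perceived quality of care. No baseline term is named there either.

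Table 1 schedules all five resident outcomes at T0, T2 and T3. The Discussion says that resident outcomes are secondary.

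**The concern.** The two sections do not say the same thing about the resident analysis. The sample size names residents among those to be analysed by ANCOVA and takes credit for a before-after correlation. The analysis section lists the resident covariates, and the term that would earn that credit is not among them. An analyst who takes the list literally would fit a model of post-intervention scores only.

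Two things are at stake, both for secondary outcomes. First, resident effects would be estimated less precisely than the data allow. Second, with only nine units per arm, a chance difference in baseline challenging behaviour or quality of life could be sizeable, and it would stay in the effect estimate.

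**Working it through.** **Inputs from the Sample size section.** Alpha 0.05 (two-sided assumed, as the article does not say), power 0.80, difference 4 points (staff Emotional Exhaustion), correlation r = .6, ICC 0.05, 121 per group in 8 units per arm. The final size is 135 per group in 9 units per arm.

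**The plan's own figure.** The usual formula is n per group = 2 × (z sum)² × SD² / difference² × (1 − r²) × [1 + (m − 1) × ICC], where m is the number of people per unit. No SD is given, so 121 cannot be reproduced from the stated inputs. It can be solved backwards:

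- z sum = 1.960 + 0.842 = 2.802, squared 7.85
- 1 − r² = 1 − 0.36 = 0.64
- m = 121/8 = 15.125; design effect = 1 + 14.125 × 0.05 = 1.706
- SD² = 121 × 16 / (2 × 7.85 × 0.64 × 1.706) ≈ 113, so SD ≈ 10.6 and the standardised difference is 4/10.6 ≈ 0.38

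This SD belongs to a staff scale and says nothing about residents. The comparison below does not need it.

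**Effect of leaving out the baseline score.** Assume that the ICC and design effect are the same with and without adjustment. The residual variance with baseline is then 0.64 of the variance without it. The standard error without baseline is larger by 1/√0.64 = 1.25, that is 25%, and the expected test statistic is multiplied by 0.8.

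Take a hypothetical resident effect that has 80% power at 121 per group under ANCOVA:

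- 121 per group, without baseline: Φ(2.802 × 0.8 − 1.960) = Φ(0.281) = 0.61
- 135 per group (m = 15, design effect 1.70), with baseline: expected statistic 2.802 × √(135/121 × 1.706/1.70) = 2.965, so Φ(2.965 − 1.960) = 0.84
- 135 per group, without baseline: Φ(2.965 × 0.8 − 1.960) = Φ(0.412) = 0.66
- Size needed to restore 80% without baseline: 121/0.64 = 189.06, so about 190 per group

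The loss is 19 percentage points at 121 per group and 18 at 135. With a t reference on 2 × (units per arm − 1) degrees of freedom, power goes from 0.74 to 0.55 (8 units per arm) and from 0.79 to 0.61 (9 units per arm). The levels are lower but the loss is about the same.

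**Sensitivity to the correlation.** The .6 is assumed within the staff calculation, and the article gives no correlation for any resident scale. For an effect with 80% power under ANCOVA at each correlation, power without baseline is Φ(2.802 × √(1 − r²) − 1.960):

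| r | power without baseline |
|---|---|
| .3 | 0.76 |
| .4 | 0.73 |
| .5 | 0.68 |
| .6 | 0.61 |
| .7 | 0.52 |

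**The case against.** A reader might infer that the plan excludes baseline adjustment for residents and so gives up about a fifth of their planned power. The article does not support that, for two reasons.

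First, the Data analysis section is silent on the resident baseline score; it does not rule it out. The staff covariate sentence has the same form and also omits the baseline score, because the ANCOVA was defined just before it. The resident sentences can be read as continuing that ANCOVA with other outcomes and covariates. The Sample size section and the T0 measurements in Table 1 fit this reading, and a multilevel model could also use T0.

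Second, there is no planned resident power to lose. The 4-point effect belongs to a staff burnout subscale. No effect size, SD, correlation or power is given for any resident outcome, so both the .6 and the 80% are borrowed. At a correlation of .3 the loss would be only 4 points.

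Both arguments stand, and they make the power figures conditional.

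A third argument is that an article may leave covariate lists to a fuller document. It carries less weight here, because the article does give the resident list, and that list lacks the term on which its own sample size relies. For staff, the preceding sentence supplies the baseline score; for residents, no sentence in the section does so expressly.

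**Conclusion.** The point holds as a mismatch between two sections that should be settled in writing. Residents are sized for an ANCOVA that uses the before-after correlation, while the stated resident covariates omit the baseline score. Followed as written, the list gives less precise secondary comparisons that remain open to chance imbalance between nine units per arm.

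The size can only be illustrated. At a correlation of .6, the standard error is 25% larger and power drops from 80% to about 61% at 121 per group, or from 84% to 66% at 135. Over correlations of .3 to .7, power without baseline runs from about 76% to 52%. This rests on a two-sided test, on an unchanged ICC and design effect, and on carrying the 80% target, and for the main figures the .6, from staff to residents. It does not show that a stated resident power target is missed. The primary staff analysis, for which baseline adjustment is stated, is not affected.

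**What to change.** In the Data analysis section, state that each resident outcome measured at T0 (NPI-NH, CMAI, Qualidem, RISE and perceived quality of care) is analysed in the multilevel model with its own T0 score as a covariate, in addition to age, sex and length of stay. This brings the section into line with the sample size section.

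Add how replacement residents are handled. The Process evaluation section registers the replacement of residents who die or relocate, and someone who enters after T0 has no T0 score.

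The cost is a sentence or two of text. The baseline measurements are already scheduled, so no further participants or assessments are needed. The small downside is that the rule for replacement residents has to be decided and written down.

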Besides the quality of the studies, there is also a problem with the description of the educational programs. These were often poorly or not described so we are unable to judge the quality of these programs. Some of the studied programs did not combine knowledge with skills training [11,15,16]. Furthermore, because of the lack of description of the follow up sessions, it is not possible to evaluate whether the programs were tailored enough. An educational program has to support various learning styles of the participants [39-41]. Studies about learning styles of nurses found that (student) nurses have a mix of all learning styles [39,40], but that more than half have a predominantly concrete learning style and almost half a reflective learning style [42]. This implies that training generally has to be interactive and multifaceted [39-41].

An important factor needed for sustaining the results is integrating the educational program in daily practice by tailoring it to individual needs and the needs and interest of the care-organization [37]. We hypothesize that implementation of an educational program that does not have the aforementioned shortcomings will more likely result in a decrease of distress experienced by the nursing staff and a decrease in frequency of challenging behavior. Therefore, we developed an educational program for nursing staff on challenging behavior that is tailored to the wishes and needs of the care-organization and combines various learning styles.

The aim of our study is to determine, in a randomized design that accounts for clustering within units, the effect of a new educational program in the short and in the mid- term on stress experienced by nursing staff (primary outcome), emotional workload, work satisfaction, stress reactions at work and knowledge about the origin and the management of challenging behavior of nursing staff and challenging behavior of the residents. We will also determine the effect of the program on Quality of Life (QoL) and social engagement of residents as stress and work satisfaction may influence the way residents are treated by nursing staff. Possibly intervening factors such as attitude about people with dementia, the organizational culture, the time residents have lived on the unit and the time nursing staff works on the unit are measured as well.

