## Methods

### Design

The TENSE-study is a cluster-randomized, controlled study on dementia special care units (DSCU) of Dutch nursing homes from different regions of the Netherlands. Nursing homes will participate after consent of the management, the unit managers, nursing staff, the board of representatives of residents and the psychologist. Eighteen units (clusters) will be randomized with a block size of 2. From each of 9 nursing home organizations, two units are included, one of which becomes an intervention unit (receives a training program) and one becomes a control unit (no training, continuing usual care). This results in nine intervention units and nine control units. Allocation to intervention or control was determined through the tossing of a coin by an independent researcher unfamiliar with the study and blinded for the nursing homes. To prevent contamination, the nursing homes need to agree that the control and the intervention unit do not have the same physician and psychologist and that nursing staff members are not employed at both units during the study period. Units are preferably at a different location.

The duration of the follow-up will be 9 months. A 3-day course (three times 2,5 hours) for intervention units will be held immediately after baseline (T0), with follow up sessions after three and six months. Assessments will take place at baseline (T0), immediately after the course (T1), just before follow up session 1 (T2), and nine months after the 3 day course (T3). Table 1 gives an overview of the measurements (see Figure 1).

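### Units are randomised in pairs within nine organisations, but the stated model has no organisation term, so the treatment SE is too large if organisations differ

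*Protocol article*

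**What the plan says.** The Design section of the protocol article fixes a pair-matched cluster design: "Eighteen units (clusters) will be randomized with a block size of 2". The pair is the organisation: "From each of 9 nursing home organizations, two units are included, one of which becomes an intervention unit". The outcome is balanced: "This results in nine intervention units and nine control units".

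The Data analysis section describes the model. Each outcome is analysed "in an ANCOVA analysis in which outcome score is the score after intervention controlling for the score before the intervention". For staff, "Age, sex and time working on the unit will be used as covariates"; for residents, "Age, sex and length of stay will be used as covariates". The hierarchy is given as "multilevel linear regression and multilevel logistic regression analyses on units, individual nurses and residents will be used". The aim at the end of the Background points to the same structure: "in a randomized design that accounts for clustering within units". The Sample size section uses one ICC, 0.05. No section puts the organisation or the pair into the model, whether as a level, a random effect or a stratum.

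**The concern.** Treatment varies within organisations, so whatever the two units of one organisation share cancels from the treatment contrast. A model that knows only units and individuals does not see this. It counts the shared part as ordinary between-unit variation and carries it into the SE. Confidence intervals are then wider than the data warrant, and the test rejects too rarely under the null.

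The protocol gives reason to think that organisations may differ. It measures organisational culture as a possible influence, and it tailors the programme to each care organisation's work processes and forms. With only 18 clusters there is little precision to spare, and the Background reports that earlier studies found almost no effect on stress.

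**Working it through.** **Inputs from the protocol article.** 9 pairs and 18 units (Design). 135 staff and 135 residents per arm in 9 units, so 135/9 = 15 per unit. ICC 0.05, correlation 0.6, alpha 0.05, power 0.80, effect 4 points, 121 per arm before the extra unit (Sample size).

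**Assumptions.** Two-sided alpha; equal unit sizes; the full ICC of 0.05 remains after adjustment; the share s of the ICC that lies between organisations is unknown and is varied.

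**The plan's own figure.** The 121 per arm cannot be confirmed, because no SD is given. With n = 2 × (1.960 + 0.842)² × SD²/4² × (1 − 0.6²) × (1 + 14 × 0.05), n = 121 requires SD ≈ 10.65. Other readings of the calculation imply SDs from about 8.2 to 12.0. The SE ratios and true sizes below do not use the SD; the power figures and interval widths do.

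**SE.** As a fraction of total variance, a unit mean has variance 0.05 + 0.95/15 = 0.1133. Pairing removes 0.05s. The ratio of the unit-only SE to the within-pair SE is therefore √(0.1133 / (0.1133 − 0.05s)):

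- s = 0.25: √(0.1133/0.1008) = 1.06
- s = 0.50: √(0.1133/0.0883) = 1.13
- s = 0.75: √(0.1133/0.0758) = 1.22
- s = 1, the limit: √(0.1133/0.0633) = 1.34

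**Size and power.** These come from simulated trials analysed on unit means (at least 200,000 per setting for the unit-only and paired tests). The adjusted SD is 10.65 × 0.8 and the effect 4 points. The unit-only test has 16 degrees of freedom (df). The fully paired test has 9 − 1 = 8. The random intercept sets a negative organisation variance to zero but keeps 8 df.

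| Organisation share of ICC | SE too large by | True size, unit-only | Power, unit-only | Power, fully paired | Power, random intercept, 8 df |
|---|---|---|---|---|---|
| 0% | 0% | 5.0% | 79% | 74% | 78% |
| 25% | 6% | 3.9% | 81% | 79% | 82% |
| 50% | 13% | 2.9% | 82% | 83% | 85% |
| 75% | 22% | 2.1% | 83% | 89% | 89% |

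The fully paired test holds 5.0% throughout. The random intercept with 8 df has size between 5.0 and 5.7%, highest at share zero. If the df return to 16 whenever the organisation variance is estimated as zero, which happens in half of trials at share zero, size there is about 6.4%.

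**Interval width.** At a half share the 95% half-width is 2.120 × 1.352 = 2.87 points for the unit-only analysis and 2.306 × 1.194 = 2.75 for the fully paired one. At share zero it is 2.87 against 3.12.

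**Sensitivity to the ICC.**
- ICC 0.02, half share: √(0.0853/0.0753) = 1.06, and the fully paired test has just under two points less power than the unit-only test.
- ICC 0.10, half share: the SE is 21% too large, true size is 2.2%, and power is 67% unit-only against 75% paired.

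**The case against.** The strongest objection is that this is one paragraph of a condensed article. It names a family of models, and a fuller plan may include the organisation. That lowers certainty about what will be run. It does not remove the point, because the article itself states the levels and the covariates, and those do not match the randomisation that it describes.

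The organisation share may also be low. The Design section requires separate physicians, psychologists and nursing staff for the two units, and prefers different locations. The baseline score will absorb part of any stable difference between organisations. This stands: the gain is of unknown size and could be near zero.

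Pairing also costs degrees of freedom, 8 instead of 16, so a fully paired test loses power below roughly a half share. This stands too, and it shapes the fix.

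A reader might infer that leaving out the pair raises the false-positive rate or makes the test invalid. It does neither; the error is in the conservative direction. A reader might also infer that the trial throws away precision that the pairing was chosen to gain. No section says why units were paired, and at a half share the fully paired interval is only slightly narrower. Nor does the interest in organisational culture prove a large between-organisation variance: the protocol speaks of culture influencing how innovations are carried out and how strong the effect is, which is largely effect modification, and pairing does not remove that.

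**Conclusion.** The point holds as a modest matter of efficiency and of calibration. The stated model does not follow the randomisation. If organisations differ at all, the treatment SE is too large and the test conservative: by 6 to 22% in the SE, with true size from 3.9 down to 2.1%, for shares of 25 to 75% at ICC 0.05. If organisations do not differ, nothing is wrong. The share is an assumption, the ICC after baseline adjustment may be below 0.05, and every power figure also rests on an SD of about 10.65 solved back from 121 per arm. The direction of the error rests on none of these. The documents do not support a claim of inflated type I error or of a large, certain loss of power.

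**What to change.** State in Data analysis that organisation, as the randomisation pair, enters every linear model as a random intercept above unit. Fix the degrees of freedom for the treatment effect in advance at the within-pair value, 8, including when the organisation variance is estimated as zero. If the software will not accept a fixed value, compute the test and interval from the estimate and its SE with t on 8 df. Report the analysis with pair as a fixed stratum alongside, since it holds 5%. Include organisation in the logistic models as well, without relying on Kenward-Roger there.

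No new data are needed, and the linear models gain one random term. If organisations do not differ, the random intercept with 8 df costs about one point of power (79% to 78%) and has size up to about 5.7%. The fully paired test then costs about six points (79% to 74%). At a half share, power rises from 82% to about 85% with the random intercept, or to 83% with the fully paired test.

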## Discussion

The TENSE-study is a cluster randomized controlled study investigating the effects of a continuous educational program on stress experienced by nursing staff (primary outcome) and emotional workload, work satisfaction, stress reactions at work and knowledge about challenging behaviour; and frequency of challenging behavior, quality of life and social engagement of residents. Client outcomes are secondary outcomes in this study. Although client outcomes are very important and have also been subject of earlier research into training programs for nursing staff, we do realize that to see an effect on client outcomes there probably has to be an effect on the outcomes for nursing staff first.

Strengths of this study are: the elaborate description of the intervention and the process evaluation in which factors that influence the study will be described. Strengths of the intervention are: tailoring the intervention to the wishes and needs of the care-organization to overcome barriers and profit from facilitators in the care-organization. The use of follow up sessions to sustain the results is positive as well. Other strengths of the intervention are the contact between the trainer and the nursing home that allows us to adjust the training program at every moment in time.

The chosen design is suitable for our purposes. It allows us to measure effects of the training program on stress and knowledge directly after the training, and the ‘short’ (3 months) and mid- term effects (9 months) by performing two additional measurements. We expect that the tailor made follow up meetings will enhance sustainability of the training results. To increase the motivation of the nursing staff, the program will be delivered to the control units when the study is finished.

The outcome measures are all commonly used in the nursing homes and they have been shown to be suitable for residents with dementia and for nursing staff. This study is one of the first nursing home studies that gathers its data by using a specifically designed website. The study has some weaknesses that should be mentioned. One limitation is that nursing staff will be aware of receiving the intervention, which may cause bias. To limit this bias, nursing staff will not be informed about the scores on the outcome measures. Another drawback is the frailty of the research population, so that the proportion of residents that dies during the research can be significant. Replacing the deceased residents may be difficult. The sample size is adjusted for the proportion of nursing staff that moves to another job. A final limitation of this study is that we are not able to study the results longer than nine months.
